## 1. Summary of the study

|                                                |                                                                                                                                                                                                                                                                                                                                                                                                                                                                                                                                                                                                                                                                     |
|------------------------------------------------|---------------------------------------------------------------------------------------------------------------------------------------------------------------------------------------------------------------------------------------------------------------------------------------------------------------------------------------------------------------------------------------------------------------------------------------------------------------------------------------------------------------------------------------------------------------------------------------------------------------------------------------------------------------------|
| Title                                          | Validation of braces designed to optimize the correction of Providence-type night braces                                                                                                                                                                                                                                                                                                                                                                                                                                                                                                                                                                            |
| Methodology                                    | Randomized, controlled, crossover and parallel design clinical trial.                                                                                                                                                                                                                                                                                                                                                                                                                                                                                                                                                                                               |
| Duration of the study                          | Patients will be followed for a period of two years                                                                                                                                                                                                                                                                                                                                                                                                                                                                                                                                                                                                                 |
| study center                                   | CHU Sainte-Justine                                                                                                                                                                                                                                                                                                                                                                                                                                                                                                                                                                                                                                                  |
| Objective                                      | Validate the new brace design method by optimizing immediate correction.                                                                                                                                                                                                                                                                                                                                                                                                                                                                                                                                                                                            |
| Number of patients                             | 58 patients                                                                                                                                                                                                                                                                                                                                                                                                                                                                                                                                                                                                                                                         |
| Diagnosis and inclusion and exclusion criteria | 
Diagnosis: Adolescent idiopathic scoliosis
 
Inclusion criteria:
 

• Aged 10 and 16 inclusively

• Thoracic/lumbar/thoracolumbar scoliosis between 20 ° and 40 °

• Risser index between 0 and 2

• <18 months after menarche

 
Exclusion criteria:
 

• Cardiovascular disease

• Neurological disorders (myopathy, neuropathy or central nervous system disorders)

• Spondylolisthesis with grade superior to 1.

• Other disease of the musculoskeletal system in the lower limbs.

• Pregnancy

 |

## 2. Context

### Importance of research

Adolescent idiopathic scoliosis (AIS) affects 280,000 young people in Canada, 66,000 in Quebec (prevalence 3-5%). Left without follow-up or treatment, it can progress rapidly during growth and severely limit the quality of life of adolescents and adults: apparent deformity, severe low back pain (73% vs 28% in those without), early osteoarthritis, cardio-pulmonary and psychological problems.

There are only **2 recognized treatments** :

- 1- for moderate AIS (Cobb 25 to 40°; 10% cases, i.e. ≈25,000/year in Canada), the **brace**, thoraco-lumbo-sacral orthosis (TLSO) in rigid plastic, renewed every 6 months and worn throughout growth,
- 2- for severe AIS >50° (1% cases, i.e. ≈2,500/year in Canada), surgery **with** instrumentation and fusion of the column is necessary, heavy treatment on the physical and psychological levels, which is considered last appeal.

#### Does the brace work?

The Scoliosis Research Society recommends wearing the TLSO 20-23 hrs/day until maturity in young people (Risser index 0 to 2), with a moderate curve (25-40°). Although used for >60 years, the effectiveness of the brace has been repeatedly questioned by the Canadian Task Force on Preventive Health Care due to lack of evidence, leading to the withdrawal of school screening for AIS in Canada. We demonstrated that this decision was harmful, causing a significant increase in patients referred too late to benefit from the brace (current 19% vs 1% at screening) with surgery as the only option, without changing useless referrals (39% vs. 37%).

In 2013, the BrAIST study, a multi-center randomized controlled trial (RCT) confirmed the effectiveness of TLSOs: 28% of treated subjects progressed beyond 50° vs 52% of untreated (OR= 1.93 [1.08-3.46] in favor of the brace). The study, which became “Gold Standard”, was interrupted by the NIH given the demonstrated superiority of the brace. A meta-analysis in 2019 reconfirmed the efficacy and safety of the treatment of idiopathic scoliosis by bracing.

For night braces, such as the Providence brace, a randomized study in 2014 demonstrated that these braces could reduce the progression of scoliosis in patients with curves below 25 degrees. More recently, a literature review and meta-analysis showed that night braces had a success rate of 78.7% versus 73.2% for full-time braces such as TLSO braces. The latest data in the literature therefore show that there is a clinical equivalence in the treatment with a TLSO brace and the night brace.

#### New paradigm for brace-optimized treatment of adolescent idiopathic scoliosis

The brace is useful but its effectiveness is not optimal, which is why our team proposed a research project with the Canadian Institutes of Health Research to optimize the treatment by brace of idiopathic scoliosis of the teenager

As part of a grant obtained from the Canadian Institutes of Health Research (Foundation grant no. 375116, 2016-2017), [name] team aimed through the proposed project to correct three deficiencies observed in the clinic during the brace treatment; 1- The number of patients needed to treat to achieve success is high due to the inability to predict which AIS will progress, 2-

Correction under brace is incomplete, 3- There is a significant problem with adherence to treatment . The general objective of [name] program was that within 7 years, brace treatment would be radically changed by doubling the % of success compared to the % of subjects needed to be treated, by the implantation of a platform unique and innovative treatment for specific and optimized care for each child. More specifically, two of the sub-goals were to increase treatment adherence (number of hours the brace was worn) by 50% and to increase the success rate of the brace by 20% using our innovative design technique. and Computer Aided Manufacturing (CAD/CAM) and finite element simulation (BraceSim). To date, the first sub-objective has been achieved through the development and validation of the first instrument for measuring functional, physical, emotional and social well-being under brace (MOBI questionnaire (My Orthopedic Brace Inventory)). This is used to identify the elements associated with non-adherence and was validated as part of a study at the CHU Sainte-Justine (project number MP-21-2018-1756 approved by the research ethic committee (CER) dated 2017 -12-06). In the continuity of this project, we wish to complete a preliminary study in order to complete the second sub-objective aiming to increase the success rate of the brace by the use of CAD/CAM technique. In recent years, our team has developed innovative methods of computer-aided design and manufacturing (CAD/CAM) based on digital simulation models personalized for each patient (brace simulator), particularly in the context of programming the Canada Research Chair in Orthopedic Engineering and [name] CRSND-Découverte subvention (CER 2018-1825). A previous randomized clinical study  by our group demonstrated that the use of CAD/CAM methods to design braces is adequate and provides immediate correction that reduces the progression of scoliosis. The results were equivalent or superior to the BrAIST  study , used as a reference in the literature. The BrAIST study demonstrated by a randomized study that wearing a brace reduced the progression of scoliosis compared to observing progression without a brace alone. Since then, our group has developed a new design and simulation model described in more detail in section **Error! Reference source not found.**

### 3. Review of relevant literature and work of our team

#### 3.1. Evaluation of scoliotic deformities

Traditionally, the evaluation of scoliotic deformities is made by physical examination and with frontal X-rays. The usefulness of 3D reconstruction for the study of scoliosis is now widely accepted  . Our research team was a pioneer in this field by developing an innovative technique for taking calibrated postero-anterior (PA) and lateral radiographs allowing the 3D reconstruction of the internal geometry of patients with an error of  $3.3 \pm 3.8\text{mm}$   .

This technology has been adopted and integrated to the EOS low-dose radiology system^19, an innovative technology developed in France (BioSpace, Inc) in collaboration with our team  . The EOS system eliminates the positioning and calibration system, and we have demonstrated that it produces x-rays 8 to 10 times less irradiating than conventional digital x-ray systems  . The evaluation of scoliotic deformities is made using computer tools allowing the calculation of different measurable 3D indices with low variability  . Our user-friendly software (Clindexia)  automatically measures 2D and 3D geometric indices of the spine, pelvis and trunk.

The complete characterization of scoliotic deformities also requires the study of the external geometry of the patient's trunk. This is essential since improvement in the aesthetic appearance of the trunk is the most important criterion for which patients with AIS desire improvement and consent to treatment 24,25 .

### 3.2. Development and validation of a computer tool for the design and manufacture of braces

The different modes of mechanical action of braces come down to the application of moments or forces on the trunk 26 since the spine is not directly accessible. How these forces are transferred to the spine is poorly documented. A few studies have measured the forces generated by the Milwaukee brace using mechanical sensors 27,28 , and those generated by the Boston brace using pneumatic and electronic sensors 29,30 . However, these studies do not present the localization of the forces at the orthosis-skin interface, nor the variation of these forces according to the position of the patients, aspects necessary for understanding the biomechanics of the orthosis.

Our team has developed a system made up of force cells connected to an electronic acquisition unit for storing data during the measurement of the tensions in the belts 31 , and we have demonstrated that the prescribed tension is very variable according to the subjects and varies greatly depending on the position of the subjects. We have also carried out the first prospective clinical study 32 to integrate the combined effect of the various parameters of the braces, i.e. the location and size of the support sites as well as the forces present, the tension of the straps and the 3D correction. obtained. Several unfavorable points of action were noted, in particular on the abdomen, at the lumbar level and posteriorly on the thorax, but on the side opposite to the deformation of the ribs. These observations may explain why there is not always a significant correction and agree with our clinical results on the 3D evaluation of the Boston brace 33 .

It is all of this work that led us to develop a computer tool for the design and adjustment of braces, integrating 3D reconstruction by x-rays, 3D reconstruction of the surface of the trunk and the brace as well as the measurement of the pressures generated by the brace on the thorax of scoliotic patients, with the aim of helping the clinician to improve the brace treatment by allowing him to visualize on screen the superimposed geometries of the bony structures, the surface of the trunk and of the brace in real time. This computer tool called Cosmescia 34 has been validated and used to perform a prospective, randomized clinical study comparing immediate 3D correction of scoliotic deformity in a group of 48 subjects with AIS whose Boston brace was adjusted with Cosmescia versus a control group whose adjustment was done by the conventional clinical method. This randomized study has clearly demonstrated that the developed tool produces better correction compared to the conventional method and that it allows for the first time a significant improvement in the 3D correction of scoliosis. These are very encouraging and exciting results that support the continuation of our research program and the upcoming dissemination of this tool in clinical settings as well as its commercialization. However, the tool remains complex to use and must be simplified for clinical use.

Over the past two decades, new methods of manufacturing braces have been developed using computer-aided design and manufacturing (CAD/CAM) techniques. The manufacturing principles are similar to conventional methods, but are computerized. The outer surface of the patient's trunk is scanned by scanner and sent to software which the orthotist can use to draw/modify the shape of the brace. A 'positive' of the shape is then generated by a computer-aided milling machine and the brace is thermo-formed on this positive. CAD/CAM is faster and produces braces that are as effective as the conventional method , making it a very promising biomedical field that remains underdeveloped in Canada.

Lagarrigue ([www.lagarrigue.com](http://www.lagarrigue.com)), one of the 2 largest orthotics-prosthetics companies in France, has created such CAD software, Rodin4D, and it has partnered with Boston Brace, one of the largest manufacturers orthoses in the USA, to manufacture braces distributed in Europe and America. It seemed only natural to our team to join forces with these companies to continue our research and develop a new platform for the generation of orthoses, within the framework of an NSERC-Strategic Program grant (STPGP 380992 -09).

This manufacturing technique is now frequently used throughout the world .

### 3.3. Development of a brace simulator

Faced with the complexity of the anatomical structures of the trunk, the development of biomechanical modeling by finite elements has made it possible to study the interactions between the spine and the thorax , to analyze scoliotic deformations  and allowed us to simulate their orthotic treatment . A detailed biomechanical model of the trunk, personalized to the geometry of each patient, was developed by our team, including the vertebrae, the pelvis, the rib cage, the costovertebral joints, several ligaments as well as the main muscles . The adequacy between the 3D geometry predicted by the model and the geometry of the patient in his orthosis made it possible to justify the use of the model to simulate the action of the braces and to study the mechanisms of correction and the contribution of the different forces applied to the trunk . Based on these studies, a treatment approach was proposed and was simulated, demonstrating that it is possible to obtain a better 3D correction by modifying the location of the support points. An optimization approach was developed and integrated into the model in order to find the location, orientation and magnitude of the forces on the trunk allowing an optimal correction. We continued these analyzes by developing a detailed explicit modeling of the brace and its interface with the trunk , in order to simulate the installation of a brace on a patient . This model makes it possible to evaluate the effectiveness of a brace even before its manufacture. We can therefore identify any shortcomings in the design of a brace and correct them iteratively in order to optimize its effectiveness. The model makes it possible to predict what will be the geometric corrections of the scoliotic deformities inside the brace. The amplitude and location of the pressures exerted by the brace on the patient's trunk can be calculated in order in particular to detect any areas of discomfort. The model also analyzes the effect of the brace on the pathological pressures exerted on the vertebral growth plates, making it possible to estimate its capacity to halt the progression of scoliosis in the long term . This model was used to evaluate the design parameters of a brace having the most influence on its effectiveness, thanks to an experimental plan where more than 12,000 braces were tested. The importance of the position of the trochanteric extension and of the opening (posterior or anterior) was particularly underlined. Finally, the link between the immediate

correction generated by the brace and its long-term effect, ie its ability to prevent the progression of scoliotic deformities, has been demonstrated from a biomechanical point of view. A strong correlation between the immediate correction of the Cobb angle of the frontal curves and the correction of the asymmetry of the pressures on the growth plates has been found .

### 3.4. CAD/CAM of braces:

Thanks to an agreement with the industrial partners Lagarrigue in France, Boston Brace in the USA and Orthèses-Prothèses Rive-Sud in Montreal, developed within the framework of the NSERC Strategic Program grant, we have coupled our 3D trunk reconstruction system (EOS and surface scanner) and our brace simulator to the CAD/CAM software (RODIN 4D) from Lagarrigue, so that we have a platform allowing the design/simulation/optimization and computer-aided manufacturing of TLSO orthoses. This CAD/CAM platform provides a synthesis of the various advanced technologies developed by the industry and by our research group in order to improve the effectiveness of brace treatment .

## 4. Objective and assumptions

**The general objective** of the project is to validate the new CAD/CAM brace design method integrating the optimization of immediate correction.

**Primary Hypothesis (H1)** : After 1 year and 2 years of use, the out-of-brace correction, as measured by Cobb's angle, from the Test braces will be non-inferior to the Control braces. The non-inferiority margin will be 5 degrees.

**Secondary hypothesis (H2)** : The immediate and medium-term (1 and 2 years) failure rate of treatment will be 10% lower for Test braces compared to Control braces. There are three different types of failures:

1. Mid-term failure (1 and 2 years) – relative progression : A progression of the out-of-brace Cobb angle of 5 degrees or greater than the value measured at visit 1.
2. Intermediate (study duration) failure – absolute progression : A progression of the Cobb angle of the main off-brace curvature to greater than 45 degrees (SRS failure criterion).
3. Medium-term failure (duration of the study) – surgery : Stopping treatment with a brace and a decision to have surgery (AVBGT or fusion).

**Secondary hypothesis (H3)** : The quality of life of patients wearing Test braces in the medium term, as measured with the SRS-22r questionnaire, will be non-inferior to that of patients wearing control braces. The non-inferiority margin will be 10%.

**Secondary hypothesis (H4)** : The immediate in-brace correction of the Cobb angle of the Test brace will be no less than that of the control brace. The non-inferiority margin will be 5 degrees.

The effects measured (dependent variables) are as follows:

| Effects measures                                                         | Descriptions                                                                           |
|--------------------------------------------------------------------------|----------------------------------------------------------------------------------------|
| Major                                                             |                                                                                        |
| Cobb angle off brace (Initial, 6 months, 1 year, 2 years).               | Measure using low-dose EOS radiography to assess the evolution of scoliosis.           |
| Secondary                                                         |                                                                                        |
| Cobb angle in the brace. (Initial)                                       | Measure using digital radiography to assess the immediate corrective effect of braces. |
| Treatment failure rate (Initial, 6 months, 1 year, 2 years)              | See failure criteria in section 6.5                                                    |
| The lordosis and kyphosis effect of the brace (Initial, 1 year, 2 years) | The angles of the curves in the sagittal plane will be measured on the x-ray images.   |
| The number of hours wearing the brace per day (Initial, 1 year, 2 years) | A compliance monitor will measure the rate of brace use.                               |
| The patient's quality of life (Initial, 6 months, 1 year, 2 years)       | The quality of life of patients will be calculated from the SRS-22r questionnaire      |

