## **7. Randomization**

Patients who meet all the inclusion criteria and no exclusion criteria will be randomized twice independently.

Randomization #1 will be to determine the trial sequence of brace types at Visit #2. Randomization #1 allocation will have a 1:1 ratio for the “test:control” sequence and the “control” sequence. : test ”.

Randomization #2 will be to determine the brace type the patient will use for a period of two years after the visit. The allocation will have a ratio of 1:1 for test and control brace type respectively.

The randomization will be done by the URCO nurse coordinator according to a block allocation of 2, 4 or 6. Neither the engineers nor the orthopedist nor the orthotist will know the brace assigned for phase #2 until these are designed, manufactured and adjusted.

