## 8. Statistical analysis plan

### 8.1. Sample size justification

The sample size was calculated to be able to accept the main hypothesis (H1) with a probability of 5% of committing the type I error and a power of 80%. The calculation was performed with nQuery software (GraphPad Software DBA Statistical Solution, San Diego, CA) and the following parameters were used:

- Significance level  $\alpha = 5\%$
- Allocation ratio  $k = 1$
- Margin of non-inferiority  $\delta = 5^\circ$
- standard deviation  $\sigma = 7^\circ$ 
- Power  $(1 - \beta) = 80\%$

The sample size should be 25 per group, so a total of 50 patients. On the other hand, a loss to follow-up of 15% is anticipated. We will therefore need 29 patients per group for a total of 58 patients.

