### 8.3. Analysis of primary hypothesis H1

The analysis of primary hypothesis H1 will have the off-brace Cobb angle as the dependent variable and the type of brace worn as the independent variable. The 95% confidence interval of the difference in correction between the test brace and the control brace will be constructed and compared to the non-inferiority margin.

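### H1 claims non-inferiority at both 1 and 2 years, but the 80% power is for one comparison and no primary visit or both-visits rule is stated

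*Protocol*

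**What the plan says.** Protocol section 4 sets H1 at two times, "After 1 year and 2 years of use, the out-of-brace correction", with one margin: "The non-inferiority margin will be 5 degrees". The table of measured effects in the same section lists the major outcome as "Cobb angle off brace (Initial, 6 months, 1 year, 2 years" and singles out no visit.

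Protocol section 8.1 ties the sample size to accepting H1 "with a probability of 5% of committing the type I error and a power of 80" per cent. It uses one alpha, one SD (7 degrees), one margin (5 degrees) and equal allocation. The result is "The sample size should be 25 per group, so a total of 50 patients". Because "a loss to follow-up of 15% is anticipated", this is raised to 29 per group, 58 in all.

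Protocol section 8.3 describes one 95% confidence interval for the test-minus-control difference, which is to be "compared to the non-inferiority margin". It names no visit and gives no rule for results that differ between visits.

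**The concern.** A hypothesis that must hold at 1 year and at 2 years consists of two comparisons. A trial with 80% power for each has less than 80% power for the pair, unless the two results are perfectly correlated or one of them is almost certain to succeed. Section 8.1 attaches its 80% to H1 as a whole, yet its inputs describe one comparison.

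The practical risk is a split result. If the interval clears the margin at one visit and not at the other, sections 4 and 8.3 do not settle whether H1 is accepted, and the decision would be made after the data are seen. This goes beyond detail that could be left to a separate analysis plan: the two visits stand in the primary hypothesis itself, and the sample size depends on how they combine.

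**Working it through.** **Inputs from the protocol.** Margin 5 degrees (section 4). SD 7 degrees, alpha 5%, power 80%, 25 evaluable per group, 15% loss (section 8.1). Allocation 1:1 (sections 7 and 8.1). A 95% interval for the decision (section 8.3).

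**Assumptions not in the protocol.** True difference 0. Correlation rho between the 1-year and 2-year test statistics, shown from 0.5 to 0.9. The same SD and the same n at both visits, varied in step 5. Normal approximation.

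**1. The protocol's own figure.** n per group = 2 × [SD × (z(1−alpha) + z(power)) / margin]².
- One-sided 5%: 2 × [7 × (1.645 + 0.842) / 5]² = 24.2, rounded up to 25. This reproduces the stated number, for a single comparison.
- One-sided 2.5%: 2 × [7 × (1.960 + 0.842) / 5]² = 30.8, rounded up to 31. This does not.

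The protocol does not state sidedness, but its sizing basis is therefore one-sided 5%.

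**2. Power at one visit, 25 per group.** SE = 7 × √(2/25) = 1.98 and 5/1.98 = 2.525.
- One-sided 5%: Φ(2.525 − 1.645) = 81.1%.
- 95% interval, which is one-sided 2.5%: Φ(2.525 − 1.960) = 71.4%.

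The gap of 81.1 − 71.4 = 9.7 points exists with one visit alone.

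**3. Power when both visits must succeed.** Joint power = Φ₂(b, b; rho), the bivariate normal probability, with b = 2.525 − z(1−alpha).

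| rho | one-sided 5% | 95% interval |
|---|---|---|
| 0.5 | 70.2% | 57.4% |
| 0.7 | 72.7% | 60.7% |
| 0.8 | 74.2% | 62.7% |
| 0.9 | 76.2% | 65.3% |

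On the sizing basis, the second visit costs 81.1 − 76.2 = 4.9 to 81.1 − 70.2 = 10.9 points.

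**4. Evaluable n per group for 80% joint power.** At one-sided 5%: 32, 30, 29 and 28 for rho 0.5, 0.7, 0.8 and 0.9. Dividing by 0.85 and rounding up gives 38, 36, 35 and 33 enrolled per group, against 29 planned.

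**5. Unequal visits.** Loss may build up over two years, so more than 25 per group could be seen at 1 year. Keeping n 25 and SD 7 at 2 years, at one-sided 5% and rho 0.5-0.9:
- 29 per group and SD 7 at 1 year: 73-79%.
- 27 per group and SD 6 at 1 year: 77-81%.
- 27 per group and SD 5 at 1 year: 80-81%.

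The 1-year values of 27 per group and SD 5 or 6 are illustrations. The protocol gives no SD or number by visit.

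**6. Type I error if either visit were enough.** Error = 1 − Φ₂(z(1−alpha), z(1−alpha); rho). With the 95% interval it is 4.5% at rho 0.5 and 3.5% at rho 0.9. At one-sided 5% per visit it is 8.8% and 6.8%. If both visits are required, the error does not rise.

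**The case against.** **The two-visit effect is modest.** Both visits measure the same patients, so a high correlation is plausible. At rho 0.7-0.9 and one-sided 5% the loss is about 5 to 8 points, and step 5 shows that it can nearly vanish if the 1-year comparison is more precise. This stands. The 70-76% is the equal-SD, equal-n case and not a general result.

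**The 57-65% mixes two problems.** A reader might infer that having two visits takes power from 81% to below two thirds. The protocol does not support that. About 10 points of the fall come from sizing at one-sided 5% and deciding with a 95% interval, and would remain with a single visit.

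**The type I error.** A reader might also infer that H1 could be claimed on whichever visit succeeds, with an inflated error. Section 4 joins the visits with "and" and nowhere says that one is enough; that reading comes only from the silence of section 8.3. Even then, the section 8.3 interval gives 3.5-4.5%, above 2.5% but below the 5% in section 8.1. The 6.8-8.8% would need a 90% interval, which section 8.3 does not use.

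**A separate analysis plan may name the visit.** It may. But H1 itself fixes two visits, and section 8.1 attaches a power to H1 that was calculated for one. That conflict lies within the protocol.

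**Conclusion.** The point holds. H1 is stated at two visits and sized as one comparison, and the protocol gives neither a primary visit nor a rule for combining the two. On the literal reading, the stated 80% is not the power of H1. It is about 70-76% at 25 per group and one-sided 5%, assuming no true difference, rho 0.5-0.9, and equal SD and n at both visits, and it comes closer to 80% if the 1-year comparison is more precise. The 57-65% under the 95% interval is arithmetically right, but it should be read against a single-visit power of 71.4%. No rise in type I error is established. Confidence is high that the text is inconsistent and moderate about the size of the loss, because the correlation and the visit-specific SD and n are not in the protocol.

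**What to change.** Choose one of two courses.

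- **One primary visit.** In H1 (section 4) and in section 8.3, name a single primary time point and make the 1-year and 6-month comparisons supportive, outside the decision on H1. Two years fits the phase 2 treatment period. The 25 per group then remains valid at one-sided 5%. The cost is wording, and 1-year non-inferiority is no longer a primary claim.
- **Both visits required.** Say so in section 4 and section 8.3, and restate the power in section 8.1 as joint power with the assumed correlation and the SD and n at each visit. The cost is a less favourable stated power, or a larger sample: 28-32 evaluable per group at one-sided 5% for rho 0.9 down to 0.5, under equal SD and n.

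Neither course cures the mismatch between one-sided 5% sizing and the 95% interval. With one primary visit, power under section 8.3 stays at 71.4% until that mismatch is resolved separately.
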